#### Eligibility criteria

Children will be eligible if they have an acute burn injury of any depth (except superficial burns), are aged from 4 to 16 years, and speak English. Children will be excluded if they have deafness, cognitive impairment, a diagnosed severe psychiatric disorder, involvement with child safety or disability services, need for ventilator support, general anaesthesia requirement for their first dressing change, or a large total body surface area (TBSA >10%). Parents of children will be eligible if they speak English. Clinicians will be eligible if they are responsible for changing child participants’ burns dressings during the study period.

##### Special considerations

Despite the absence of agreement on contraindications to hypnotherapy, screening for patients with cognitive deficits or severe psychiatric disorders is important as they may not be responsive or comfortable with the experience [33]. These patients will be identified by clinicians based on comorbidities or routine psychosocial screening (i.e. collection of data on diagnosed psychiatric disorders) before being approached for recruitment.

### Intervention

Hypnosis is established with an induction procedure to enhance responsiveness and reduce peripheral awareness followed by delivering suggestions within a specific sociocultural context to guide participants to experience cognitive, sensory, motor, or perceptive alterations [34, 35]. Whereas the term *hypnosis* is used to describe the hypnotic process, *hypnotherapy* or *clinical hypnosis* refers to the therapeutic use of hypnosis in medical and psychotherapeutic contexts [8, 34, 35]. Hypnotherapy is thus defined as a treatment modality using suggestions in a hypnotic context to elicit perceptual, sensory, motor, and cognitive changes for therapeutic purposes [36]. The study intervention involves a pre-hypnosis interview followed by hypnotic suggestibility screening (during the first dressing change) and a hypnotherapeutic session.

#### Pre-hypnosis interview and hypnotic suggestibility screening

The pre-hypnosis interview and hypnotic suggestibility screening are intended to establish rapport, promote hypnotic responding, screen out irresponsive participants, and guide hypnotherapeutic sessions.

##### Pre-hypnosis interview

The interview is intended to clarify misconceptions about hypnotherapy; mitigate anxiety; enhance compliance, therapy expectations, and attitude; build rapport and trust; and collect information from children and parents to guide tailoring the hypnotherapeutic session [8]. The interview will be conducted based on literature regarding what can promote optimal therapy for children in pain (supplementary file 2 - table A) [8].

##### Hypnotic suggestibility screening

Hypnotic suggestibility, an important factor in response to hypnotic suggestions, will be screened for using the Stanford Hypnotic Scale for Children (SHCS-Children) immediately before children’s first dressing change (Table 2) [37]. Individuals with low hypnotic suggestibility are unlikely to benefit from hypnotherapy whereas those with high suggestibility show the strongest response to hypnotic analgesia and those with medium suggestibility have been shown to obtain pain relief [9, 38]. Therefore, only children with medium to high hypnotic suggestibility scores will be eligible for hypnotherapy to limit participant-related confounding factors by having more homogenous participants in terms of response, potentially increasing the effects of hypnotherapy. Children with low hypnotic suggestibility scores will be excluded from the study but will continue to receive standard care to avoid exposing children who are unlikely to obtain pain relief with hypnotherapy to an unnecessary burden of hypnosis (Table 2). Low scores (below three on the standard SHCS-Children and below two on the modified SHCS-Children) were determined based on the hypnotic suggestibility literature (Table 2). Due to the great variability in response to specific suggestions, individuals with high hypnotic suggestibility may be highly responsive to some suggestions and unresponsive to others [33]. Therefore, a tailored version of the hypnotic suggestibility  scale incorporating anaesthesia suggestions will be used to assess specific responses to hypno-anaesthesia suggestions and thus inform the delivery of therapeutic suggestions [33]. Responses to test suggestions of the hypnotic suggestibility scale will be used to guide the hypnotherapeutic session by informing the hypnotherapist on children’s preferences (i.e. favourite music type and memory) and the type(s) of suggestions they are responsive to [33].

**Table 2 Tab2:** Description and psychometric properties of measures of behavioural and involuntariness responses to hypnotic suggestions

Measurement	Goal	Description	Score ranges	Scoring	Duration	Time point	Psychometric properties
Standard SHCS: CHILD form [37]	To measure behavioural responses to hypnotic suggestions for children aged 6–16 years	- Relaxation/eye closure induction; - 7 test suggestions for time regression, visualisation, ideomotor responses, and post-hypnotic suggestions to re-enter hypnosis at hand clap^a^	0–7: - Low: 0–2; - Medium: 3–5; - High: 6–7	- 0 if absent or negative behavioural response, - 1 if positive behavioural response [37]	20 mins	Just before and during the 1st dressing change	- Moderate correlation with the Stanford Hypnotic Susceptibility, Form A scale: *r* = 0.67 [37] - Established concurrent validity [37]
Modified SHCS: CHILD form [37]	To measure behavioural responses to hypnotic suggestions for children aged 4–8 years	- Active induction in which eyes can be open; - 6 test suggestions for time regression, visualisation, and ideomotor responses	0–6: - Low: 0–1; - Medium: 2–4; - High: 5–6				
Involuntariness numeric scale [39]	To rate involuntariness and automaticity experienced during the responses to SHCS: CHILD suggestions	Age-appropriate question reworded to children’s age regarding experienced involuntariness during responses to SHCS: CHILD items (*did that feel like you made that happen or that it happened by itself?)*^b^	Mean of items scores	Score ranging from 0 (no response), 1 (voluntary response to suggestions) to 5 (involuntary-automatic enactment) for each SHCS: CHILD test item	10 mins	During the 1st dressing change	- Good internal consistency (*α*s: 0.76–0.86) [40] - Adequate construct validity: moderate correlation of involuntariness scores with scores on a standardised hypnotic suggestibility scale (*r* = .49, *p* < .001, 95% *CI* = [.31, .65], *n* = 58) [41]

^a^Anaesthesia suggestion will be incorporated in the ideosensory test suggestion to assess specific responses relevant to hypno-anaesthesia

^b^Following each test suggestion, children will be asked about the involuntariness experienced during responses to test suggestions

#### Hypnotherapeutic session

Hypnotherapeutic sessions consist of induction, deepening (i.e. intensification) techniques, and therapeutic suggestions prior to counter-suggestions (Table 3). A maximum of five sessions will be provided during dressing changes that are usually performed every 3 days or weekly. Sessions will thus have the same duration as the burns dressing change, which is usually between 20 and 35 minutes. During the first dressing change, the session will be reduced to therapeutic suggestions following the standard induction included in the hypnotic suggestibility scale. Pre-recorded music will accompany sessions (supplementary file 2- table B) [8, 42]. External distractions will be minimised as much as possible with the hypnotherapist being the only person talking to the child whenever possible. Following clinical policies and to reduce separation anxiety, parents will be encouraged to be present during sessions, unless they choose not to do so [15].

**Table 3 Tab3:** Description of the phases and components of the hypnotherapeutic session

Phase	Core components	Description of components	Goal
Induction	Positioning	Ask children to be in a comfortable position for hypnosis [8].	To promote comfort and relaxation [8].
	Eye fixation and abbreviated progressive muscle relaxation	Ask children to focus their attention on the hypnotherapist’s hand while tensing their hand’s muscles for a few seconds before releasing tensions [8].	To elicit relaxation, shift of attention, absorption in hypnosis, and dissociation from the painful stimulus [43, 44].
	Eye closure	Ask children to optionally close their eyes [8].	To block external distractions and promote internal absorption [37].
	Lifting of the hand	Ask children to keep their hands in a vertical position.^a^	To promote numbness in the hand and response expectancies during glove anaesthesia.
	Deliberate faster breathwork and suggestions for relaxation	Ask children to maintain faster and deeper rhythmic breathing for a few minutes then to gradually relax body muscles following pleasant imagery suggestions (e.g. *blowing tensions away and inhaling relaxing lights*) [8].	To enhance suggestibility by inducing mental and physical relaxation; promote positive coping by distraction; establish the hypnotic context; and promote response expectancies [8, 43, 44].
	Favourite place imagery	Give suggestions for favourite place imagery with few details that allow children to project their own experiences and preferences (e.g. *imagine your favourite place*) [8].	
	Ideomotor signalling	Ask children to make a physical movement (e.g. lifting a finger) as a sign of positive response to suggestions [8].	To reflect the inner experience of children, test response to suggestions and promote children’s sense of control [8].
	Metacognitive suggestions	Notify children on the nature of subsequent procedures or what is next in the intervention [63].	To promote children’s cooperation, positive response expectancies and prepare them for subsequent intervention steps [44].
Deepening/intensification suggestions	Deepening/intensification ideomotor suggestions	Give suggestions for movement without conscious muscle activity (e.g. eyelid catalepsy, arm heaviness) then test responses to suggestions [8].	To reinforce suggestions; accentuate dissociation from the external setting, focus of attention and absorption in the hypnotic experience [8].
	Compounding suggestions^b^	Give suggestions for absorption in hypnosis accompanying physical experience and sensations (e.g. *As your hand drops back down to your side, you can slowly and gently go deeper into hypnosis*) [8].	
	Counting and stairs imagery	Give suggestions for relaxation and absorption involving visualisation (e.g. *count out-loud as you go downstairs, go deeper into hypnosis*) [8].	
Therapeutic suggestions	Hypno-analgesia and hypno-anaesthesia suggestions	Deliver direct suggestions for ideosensory alterations (e.g. numbness and coolness) [8].	To reduce pain sensations by inducing analgesia and anaesthesia [8].
		Give indirect suggestions of pleasant imagery involving regression into enjoyable pain-free past events; glove-anaesthesia technique, metaphors for dissociation or substitution of pain-related sensations, cognitions, and feelings (e.g. darkness representing discomfort is transformed into a relaxing light) [8]. N.B. Suggestions for pleasant imagery can involve a detailed description of elements to visualise to assist imagination or fewer details that enable children to project their experiences and preferences (e.g. *imagine flowers that you like*) [8].	To target sensory, cognitive, and affective components of pain by respectively inducing sensory (analgesia, anaesthesia), perceptual (altered perception and expectations) and affective (agreeable feelings, reduced pain unpleasantness) alterations; accentuate dissociation from pain and absorption in pleasant internal experience; promote relaxation, comfort, positive change, and reduced alienation; guide the use of children’s internal resources for better coping and sense of control [8, 10].
	Suggestions for positive conditioning	Describe the setting as a place for healing rather than a source of distress and portray pain as a signal of injury to be treated rather than an enemy to be defeated [8].	To promote positive conditioning involving trust and positive views towards clinicians, treatment procedures, pain, and the medical setting [8].
Post-hypnotic suggestions	Anchoring	Use “anchoring techniques” and test the response to the anchor under-hypnosis (e.g., re-experiencing itch relief at hand clap) [8].	To teach children effective ways to reduce itch and distress while promoting autonomy, confidence, and positive coping [8].
	Self-hypnosis training	Give suggestions to practise self-hypnosis at home [8].	
	Future progression	Give suggestions for pleasant future imagery using children’s preferred element as a gateway to future events (e.g. *crossing a bridge to a pleasant future*) [8].	To promote positive conditioning with enhanced comfort, relaxation, and cooperation in future dressing changes; itch relief; enhanced healing [8].
Emergence from hypnosis	Counter suggestions	Give alerting suggestions while counting; then ask children to open their eyes and gradually switch to a seated position when ready after their awareness is back to the usual state (e.g. *at the count of five you can open your eyes, feeling alert*) [8].	To remove numbness and anaesthesia while inducing alertness and switching of awareness to the external surrounding [8].
Post-hypnosis phase	Post-hypnotic talk	Invite children to ask questions and discuss their experience; debrief those with negative reactions [8].	To promote safety, trust, and positive coping [8].
	Self-hypnosis tape and test of anchoring	Test children’s response to the “anchor” and give them a recording for self-hypnosis [8].	To reinforce therapy outcomes, positive coping, and sense of control [8].

^a^Children are asked to keep their hands in a vertical position throughout the session

^b^Compounding suggestions: continuous establishing of new responses onto the foundation of past responses

##### Addressing influencing factors

For optimal treatment, the intervention will address not only pain sensations but also biopsychosocial factors of hypnotic responding (e.g. views towards hypnotherapy, context, imaginative capacities, hypnotic suggestibility) (supplementary file 2 - table C). The intervention will also be tailored to situational (e.g. cognitive, emotional, attentional, and social components of pain) and predisposing (e.g. beliefs, cultural learning, cognitive level, and past conditioning) factors of pain (supplementary file 2 - table D) [2, 17, 45–48].

#### Delivery mode, material, and provider of the intervention

For optimal therapy, individual interventions will be provided face-to-face, not via audiotape to address changes in pain, distress, itch, and perceptions of hypnosis [8, 12]. Following the initial delivery of hypnotherapy, children will be provided with a taped recording of instructions for self-hypnosis for daily practice to reduce the time needed to teach them self-hypnosis. The provider of the intervention is a certified hypnotherapist and a member of the National Guild of Hypnotists. The hypnotherapist has extensive experience (more than ten years) in conducting hypnotherapy with children from diverse backgrounds with a range of conditions involving pain and distress in therapeutic and medical settings. Phases and components of the intervention are detailed in an intervention manual that can be obtained upon request.

#### Tailoring, adaptations, and fidelity in delivery

The hypnotherapist will adhere to the manual in delivering core elements of the intervention to facilitate replication and target procedural pain, state anxiety, and itch. The fidelity in delivering the intervention will be assessed using a fidelity checklist (supplementary file 2 - table E). The intervention will be tailored and adapted as informed by the pre-hypnosis interview and hypnotic suggestibility screening (supplementary file 2 - table F) to account for the hypnotherapist’s style, children’s preferences, and factors related to children, the setting, parents, and clinicians [8].

#### Concomitant treatments

Children will receive standard care including a combination of pain medications offered by treating clinicians at least 20 min (medications’ onset of action) before the dressing change in specific dosages that are part of usual care (supplementary file 2 - table G). Active (e.g. interactive toys including video games, virtual reality devices, controlled breathing, and guided imagery) and passive distraction techniques (e.g. passive music, videos on a portable device) will also be used as part of standard pre- or post-procedural care.

### Measurements

#### Hypnotic suggestibility and involuntariness

Child participants’ hypnotic suggestibility will be assessed by measuring behavioural responses to test suggestions using the Stanford Hypnotic Scale for Children [37]. The use of the scale is based on age-appropriate content for children between 4 and 16 years and administration in previous paediatric research (Table 2) [20, 37, 49]. Involuntariness will be measured to discern whether the responses to suggestions were due to simple compliance or higher responsiveness as the experience of involuntariness is central to the classic suggestion effect [39]. Bower’s numeric scale will be used to measure the degree to which children experience involuntariness during responses to test suggestions of the Stanford Hypnotic Scale for Children (Table 2) [39].

#### Sociodemographic data and burns characteristics

Data on child participants’ sociodemographic and burn characteristics will be gathered from clinicians, hospital charts, and medical records to describe the sample and triangulate data (Table 4).

**Table 4 Tab4:** Collection of data on sociodemographic and clinical characteristics

Sociodemographic data and clinical characteristics	Dressing change time point			Source of data	Assessor	Dressing change
	Pre	Mid	Post			
Sociodemographic data: burn aetiology and site, ethnic background, comorbidities, skin type, and adjunct interventions (pain medications and first aid)			x	Patient interview	Treating surgeon or nurse	1st dressing change
Burn characteristics (burn depth, TBSA, mechanism, and site of injury)	x			Medical baseline examinations		

#### Process evaluation

Outcomes of the implementation process are outlined in Table 5. Potential effectiveness will be measured by health-related outcomes of procedural pain, state anxiety, and itch at different time points as guided by the RE-AIM outcome of *effectiveness* (Table 6). The selection of health outcomes measurement tools is based on psychometric properties, feasibility, and clinical utility for children aged from 4 to 16 years (supplementary file 3). Salivary α-amylase, a bio-indicator of the sympathetic adreno-medullary system (produced by norepinephrine-responsive salivary gland cells), will be measured as a stress biomarker. The choice of salivary α-amylase was made as the authors are experienced in administering the test rapidly in children research studies, and based on the measures’ reliability, validity, and sensitivity as a marker of distress and minor stressors [50].

**Table 5 Tab5:** Process evaluation with data collection time-points

Implementation outcome	Measurement	Dressing change time point			Source of data (measurement tool)	Assessor	Dressing change
		Pre	Mid	Post			
Reach	Rate of families willing to participate out of those approached for participation	x			Report	Hypnotherapist	1st dressing change
Acceptability	Parents’ and children’s beliefs/views on hypnotherapy	x			Field notes, semi-structured pre-hypnosis interview^a^		
	Children’s level of perceived self-efficacy	x			1–10 Likert scale		
	Children’s level of positive therapy expectations	x			1–10 Likert scale		
	Satisfaction of parents and children with suggestibility screening, involuntariness measures, and pre-hypnosis interview			x	Satisfaction NRS^b^		
	Satisfaction of parents, children, and clinicians with the hypnotherapeutic session			x	Satisfaction NRS^b^		Each dressing change
	Families’ and clinicians’ likes, dislikes, recommendations, and perceived burden of required time and effort regarding hypnotherapeutic sessions			x	Semi-structured interview^a^ and field notes		Last dressing change
	Satisfaction of families with health outcomes measurements			x	Satisfaction NRS^b^		
Effectiveness	Perceived benefits			x	Field notes, reports of children, parents, and clinicians		
	Safety of hypnotherapy (rate, timing, duration, and severity of adverse events)		x	x			Each dressing change
	Health outcomes	(Refer to Table 6 for details)					
Adoption	Rate of clinicians consenting to participate among those conducting dressing changes.	x			Report	Hypnotherapist	1st dressing change
Implementation: fidelity	Retention rate		x	x	Report on the rate of children completing the intervention		Each dressing change
	Fidelity in collecting data on health outcomes			x	Response rate in data collection forms (amount and type of missing data)		
	Fidelity in delivering the intervention			x	Study-specific checklist^c^	Independent observer expert in clinical hypnosis	
	Additional adaptations and modifications			x	Documentation of what, when, and how adaptations occurred		
Feasibility	- Adequacy of resources (adequately working music player, calm space) - Presence/absence of interruption (s) - Time availability (sufficient for delivering study procedures) [31]	x	x	x	- Field notes - Intervention pre-recording	Hypnotherapist	

^a^Following permission from children and parents to audiotape the intervention

^b^Adult participants (parents or clinicians) and children ≥ 8years will self-report their satisfaction; proxy reports will be obtained from parents for children < 8years

^c^An independent assessor (preferably hypnotherapist) will assess the fidelity of delivering the intervention through analysing pre-recordings using a study-specific checklist based on the intervention manual; % of core elements and non-core elements delivered will be reported

**Table 6 Tab6:** Health-related outcomes measured using the RE-AIM outcome of effectiveness with data collection time points

RE-AIM outcome	Health-related outcomes		Dressing change time point			Source of data (measurement tool)	Assessor	Dressing change
			Pre	Mid	Post			
Potential effectiveness	Acute procedural pain	Pain intensity	x	x retro	x	FPS-R (≤ 8 years) [51], I-INRS (≥ 8 years) [52], FLACC^a^ [53]	Hypnotherapist	Each dressing change
		Pain unpleasantness				UNRS (≥ 8 years) [52]		
	State anxiety		x	x retro	x	VAS [54]		
	Itch	Intensity			x	Itch-NRS: self-report ≥ 8 years, proxy-report < 8 years [55]		From 3rd dressing change
		Frequency				Questions on itch episodes (per week, per day) [55]		
	Physiologic measures of pain and distress	Heart rate	x	x	x	Monitoring device		Each dressing change
		Salivary α amylase (in children’s saliva samples)	x		x	ELISA kits (Stratech Scientific, Avalon NSW)	Independent observer	
	Wound healing	Duration and the total number of dressing changes until 95% re-epithelialisation	x	x	x	Medical records or reports of clinicians	Independent surgeon and nurse	
		% of re-epithelialisation		x				

*NRS* Numeric Rating Scale, *INRS* Numeric Rating Scale for Pain Intensity, *UNRS* Numeric Rating Scale for Pain Unpleasantness, *FPS-R* Faces Pain Scale-Revised, *FLACC* Face, Legs, Activity, Cry, Consolability, *retro* Retrospectively

^a^The FLACC scale will be used as a behavioural measure of child participants’ pain using nurse observation

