#### Post-intervention

Saliva samples will be collected by the hypnotherapist 10 minutes following dressing changes. Information will be recorded regarding children’s medications, time of last waking up, the last brushing of teeth, food/drink/gum intake during the previous hour, and caffeine consumption during the collection day. The date and time of collection and the volume of saliva samples will be recorded. Samples will be stored at 4°C to be spun in a centrifuge at 1400 × *g* for 10 min at room temperature and then frozen at −80°C until analysis in triplicate within 7 days. Following the collection of data on sociodemographic characteristics and process evaluation outcomes, data analysis, and synthesis will be performed.

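### The treating hypnotherapist assesses time sufficiency and apparently collects the satisfaction ratings, and both feed the progression decision

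*Protocol article*

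**What the plan says.** **Provider.** The section on delivery mode, material and provider says "The provider of the intervention is a certified hypnotherapist and a member of the National Guild of Hypnotists". The article uses the singular throughout.

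**Table 5.** The hypnotherapist is printed as Assessor in the Reach row. The Assessor cells below it are blank through Acceptability and Effectiveness, including the row for "Satisfaction of parents, children, and clinicians with the hypnotherapeutic session". The hypnotherapist is printed again for Adoption and for Feasibility. Feasibility covers interruptions and "Time availability (sufficient for delivering study procedures) [31", with field notes and a recording as sources. Footnote b states who gives the satisfaction score: "Adult participants (parents or clinicians) and children ≥ 8years will self-report their satisfaction; proxy reports will be obtained from parents for children < 8years". Fidelity of delivery goes instead to an "Independent observer expert in clinical hypnosis", who under footnote c works from recordings.

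**Table 6.** The hypnotherapist is printed as Assessor in the pain-intensity row, which lists three tools, FLACC among them. The cells are blank for pain unpleasantness, state anxiety, itch and heart rate. Footnote a, attached to FLACC alone, says it measures "pain using nurse observation". Salivary α-amylase is given to an "Independent observer", beside the assay kit. The Post-intervention section says "Saliva samples will be collected by the hypnotherapist 10 minutes following dressing changes".

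**Use of the data.** The Progression criteria section requires enough time in more than 80% of children who start hypnotherapy, and moderate to high satisfaction in more than 50% of families. The Study strengths and limitations section mentions the missing control group but not who collects the data.

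**The concern.** Feasibility and acceptability are the primary aims, and two of the six listed progression criteria draw on data that the provider assesses or apparently collects. Two mechanisms could push these data upward:

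- **Courtesy bias in satisfaction.** A family that hands its rating to the person who has just treated the child may be reluctant to mark it low. The pre-hypnosis interview is designed to build rapport and trust with that same person.
- **Self-assessment of time.** Whether the time was sufficient, and whether an interruption counts as one, is a judgement about the provider's own session.

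Both mechanisms favour a decision to proceed, and a single-arm study has no comparison group to offset them. The Design section says several sources are used to avoid relying on one; routing parent, child and clinician ratings through one interested person weakens that aim. Clinicians' satisfaction is exposed in the same way, although the progression criterion counts families only.

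**Working it through.** No stated figure is in dispute, so there is none to reproduce. The check sets the assessor entries side by side and then shows how sensitive the two thresholds are.

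**Step 1. Who assesses what**

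| Item | Assessor entry | How firm | Who determines the value |
|---|---|---|---|
| Feasibility: time, interruptions | Hypnotherapist | Printed in the row | Hypnotherapist, with recordings as a source |
| Pain intensity | Hypnotherapist | Printed in the row | Child on the self-report scales; nurse on FLACC by footnote a |
| Satisfaction | Blank; nearest entry above is Hypnotherapist | Inferred | Child, parent or clinician |
| Anxiety, itch | Blank; nearest entry above is Hypnotherapist | Inferred | Itch: child or parent; anxiety: a visual analogue scale |
| Heart rate | Blank; nearest entry above is Hypnotherapist | Inferred | Monitoring device |
| Salivary α-amylase | Independent observer | Printed in the row | Laboratory assay |
| Wound healing | Independent surgeon and nurse | Printed in the row | Records or clinicians' reports |
| Fidelity of delivery | Independent observer | Printed in the row | Checklist applied to recordings |

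Only feasibility therefore rests directly on the provider's judgement. For satisfaction, the provider is at most the person who receives the rating.

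**Step 2. Sensitivity of the thresholds (illustration)**

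Inputs: n = 30 from the Sample size section, used here both for families and for children starting hypnotherapy; thresholds from the Progression criteria section; the rates at which criteria are recorded as met are assumptions.

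- Satisfaction: 0.50 × 30 = 15, so more than 50% means at least 16.
- Time: 0.80 × 30 = 24, so more than 80% means at least 25.

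The chance of passing is P(X ≥ r), where X is binomial(30, p).

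| Satisfaction, r = 16: p | 0.40 | 0.45 | 0.50 | 0.55 | 0.60 |
|---|---|---|---|---|---|
| P(pass) | 0.097 | 0.231 | 0.428 | 0.645 | 0.825 |

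| Time, r = 25: p | 0.70 | 0.75 | 0.80 | 0.85 | 0.90 |
|---|---|---|---|---|---|
| P(pass) | 0.077 | 0.203 | 0.428 | 0.711 | 0.927 |

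From a true satisfaction rate of 45%, an upward shift of 0, 5, 10 or 15 points gives a chance of passing of 0.23, 0.43, 0.65 or 0.83. From a true time-sufficiency rate of 75%, a shift of 0, 5 or 10 points gives 0.20, 0.43 or 0.71. These figures show sensitivity near the thresholds. They do not estimate the bias.

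**The case against.** The case on the other side has real force, and several stronger readings should be set aside.

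- **A reader might infer that the provider scores nearly all the outcomes.** The tables do not support this. Satisfaction and itch are self- or proxy-reported, two of the three pain-intensity tools are self-report scales, heart rate comes from a device, and wound healing is independent.
- **A reader might infer that Table 6 contradicts itself on FLACC.** One Assessor cell covers three tools and the footnote marker sits on FLACC alone, so the footnote reads naturally as an exception. The table needs to be clearer, but a contradiction is not shown.
- **A reader might infer that table and text contradict each other on saliva.** They can be reconciled if the independent observer runs the assay and the hypnotherapist takes the sample. The article does not draw that distinction, and the Intervention phase section names nobody for the pre-procedure sample. Nor is a collector's influence on a measured concentration obvious.
- **A reader might infer that the hypnotherapist leads the final interview on likes and dislikes.** The cell is blank, and the Qualitative analysis section refers to researchers conducting the interviews without identifying them.
- **The assignment for satisfaction is an inference** from blank cells in a table extracted from a PDF, and the article does not say how forms are returned. The full protocol may say more. This stands as a limit on certainty, but no one else is named for satisfaction anywhere in the article.
- **Recordings already exist as a check on time.** Table 1 lists them as the source for available time. They reduce the risk, but Table 5 still gives the assessment to the provider.
- **All the progression criteria must be met**, so an inflated result on one of them does not by itself produce a decision to proceed. This stands: the bias matters when the other criteria are met.

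**Conclusion.** The concern holds in a limited form. The treating hypnotherapist is explicitly the assessor of time availability, interruptions and pain intensity, and apparently also collects the satisfaction, anxiety and itch ratings. The main exposure is in two progression criteria: courtesy bias in satisfaction, and the provider's own judgement of time sufficiency. The limitations section does not disclose it.

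The size of any bias is unknown. The illustration assumes 30 units, independent ratings and a chosen shift; it shows only that a shift of 5 to 10 points matters when the true rate is near the threshold. With a true rate well clear of the threshold, the same shift would change little. The point on satisfaction also depends on reading the blank cells as carried down. FLACC and saliva call for clarification of wording and are not evidence of bias. The arrangement should be changed because the remedy is cheap and the plan already uses an independent assessor for fidelity of delivery.

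**What to change.** 1. **Satisfaction.** State in Table 5 that ratings are self-completed (by the parent for children under 8), sealed, and returned to someone other than the hypnotherapist, who is out of the room. Clinicians rate satisfaction too, so a sealed form or a tablet is preferable to handing an open form to clinic staff.
2. **Time and interruptions.** Make the independent fidelity assessor the assessor in the Feasibility row, scoring both from the session recordings. Recording depends on the family's permission, so report any session without a recording separately as assessed by the provider.
3. **FLACC.** Show the nurse as scorer in the Assessor column of Table 6, in line with footnote a.
4. **Saliva.** Reconcile Table 6 with the Post-intervention section by stating separately who collects the sample and who assays it, and name the collector of the pre-procedure sample.
5. **Limitations.** State that the provider collects the remaining self-reported ratings.

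The cost is wording in Tables 5 and 6 and in the Post-intervention, Intervention phase and limitations sections, envelopes or a tablet, a little more coordination at each visit, and some extra time for the fidelity assessor, who reviews the recordings anyway.
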